### Data analysis

In accordance with Research Question 1, we hypothesize that help-seeking behavior will increase from baseline to 3 and 6 months by a greater amount in the Beyond Silence group than in the MHFA control. The primary approach to this question is the repeated measures analysis of a checklist of desirable help seeking/help providing behaviors, obtained from the survey at each time point. Overall tests of the change across all three measurements are available from generalized linear mixed-effects analysis, assuming that the count (from 0 to 20 behaviors) is distributed as a Poisson variable. This is a standard approach that accounts for over-dispersion in the Poisson model arising from the repeated measurements, permits the inclusion of participants who have not completed all three assessments, and allows for flexible modeling of the change over time and the inclusion of any relevant covariates [41]. In the primary analysis, the statistical significance of treatment group in this model will be used to address the first research question. In view of the randomized design, the primary analysis will not include additional covariates, but the model will be used to explore modifying effects by including additional covariates (e.g. age, sex, prior experience with mental illness) and interactions between these covariates and treatment group. As a secondary outcome, we will analyze a scaled measure of behavioral intentions using similar linear mixed-effects analysis.

In Research Question 2, we propose mediating forces that are expected to be different in the two programs, including scaled measures of mental health literacy (expected to be higher in the MHFA group), stigma regarding mental illness (expected to be greater in the Beyond Silence group), and attitudes towards seeking professional help (expected to be higher in the Beyond Silence group). Following recommendations by Baron and Kenny [42], we will initially explore whether changes in literacy occur in association with the interventions. These analyses will use linear regression, modeling change in literacy and stigma, respectively, occurring in association with the interventions. Next, we will use Poisson or negative binomial regression to determine whether changes in literacy, stigma and attitudes associated with intervention (as well as overall levels of each) predict counts on the desirable behavior checklist. If associations are observed in both cases, we will evaluate change in these measures using linear mixed effects as described for Research Question 1. Substantial diminishment, or disappearance, of the effect of the interventions on help-seeking when the potential mediators are included in the model will be interpreted as providing evidence of mediation.

The random assignment of participants to intervention groups eliminates biases in the evaluation of the treatment effects, but the generalizability of this effect in relation to the representativeness of the sample will be assessed by comparing demographic and employment data from study participants to the equivalent data available for the entire organization. This data also provides insight on the reach of the program within the organization in terms of the characteristics of who volunteers to participate in this kind of program. This augments the qualitative analysis of Research Question 3.

Although our primary research questions are analyzed through a clinical trial, a mixed methods approach can be particularly important for understanding program implementation. Research Question 3 addresses the process of implementation; input from program participants and leaders will add depth to our understanding of the mediators and effectiveness of implementation. First, written feedback from the post-group surveys for each intervention will be reviewed and coded to identify common themes regarding program impact, strengths and areas for improvement. Next, notes from monthly meetings with the peer educators will be reviewed to identify implementation strengths and challenges from the perspective of the facilitators [43]. Key themes from each of the programs will be compared and contrasted to understand the differential impact and critical ingredients of MHFA versus contact-based education. The qualitative data (including attendance records) could be used to corroborate (or refute) quantitative findings about the differential impact of each approach.

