The plan is to enroll 200 employees in total, with 100 participants in each group. In each of the four intake periods, we plan to include 24 to 26 participants, and will actively recruit to ensure sufficient numbers prior to randomization. Following randomization, an intent-to-treat analysis will be incorporated, including all study participants. Quantitative precision estimates suggest that this sample size is sufficient to detect any real and important benefit of CBE over literacy training on change in help-seeking behavior. Two RCT evaluations of MHFA (literacy) interventions among Australian healthcare workers found that 50% to 75% of workers reportedly offered help to a person with mental health problems, prior to the intervention [24,25]. Based on this, we expect an average of about 1–2 behaviors at baseline across the samples. To simplify, we approximate the precision to detect change in mean count from baseline to the 6 month follow-up using calculations for the linear mixed-effects model, but allowing for non-constant variance of the counts by assuming that the variance averaged over groups and occasions might be as high as 4. Also assuming high consistency of help-seeking within groups (test-retest correlation, 0.80), we have an 80% chance of finding a significant (p < .05) difference between the two groups in average change over 6 months of as little as 0.44 behaviors. That is, even if the real advantage of CBE over MHFA is very small (less than 1 new behavior, on average), we have a high probability of detecting it. The precision for estimating mediators such as changes in stigma scores is similarly high. Based on initial pilot data, there were significant increases in behavior over time therefore the projected sample size should be more than sufficient to detect change.

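### The sample-size inputs (variance 4, test-retest correlation 0.80) do not fit the planned Poisson mixed model at a mean of 1–2 behaviors, so 80% power at 0.44 is optimistic under the trial's own primary analysis

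*Protocol article*

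**What the plan says.** The Data analysis section of the protocol article bases the first research question on a generalized linear mixed model, "assuming that the count (from 0 to 20 behaviors) is distributed as a Poisson variable". It adds that the approach "accounts for over-dispersion in the Poisson model arising from the repeated measurements". No random-effects structure, dispersion parameter or standard-error method is named.

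The sample justification, under Participants, gives these planning inputs:

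- level: "we expect an average of about 1–2 behaviors at baseline across the samples"
- spread: "assuming that the variance averaged over groups and occasions might be as high as 4"
- stability: "assuming high consistency of help-seeking within groups (test-retest correlation, 0.80"

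With 100 per group, it states an 80% chance of detecting a difference in change of 0.44 behaviors at p < .05. It says openly that this is a simplified calculation from a linear mixed-effects model.

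**The concern.** A linear mixed model takes the within-person variance as a free input. A Poisson mixed model does not: given a person's random effects, the variance of a count equals its mean. Within-person variance drives the precision of a change, so the power statement and the primary test should agree on it, and here they do not.

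Three outcomes are possible:

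- If the Poisson model is right, the stated power is not available.
- If the planning values are right, the Poisson standard errors are too wide and power is lost.
- If counts vary within a person by more than Poisson allows, the standard errors are too narrow and the type I error rises.

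The sentence on over-dispersion does not settle this. Random effects for persons absorb spread between people; they do not free the occasion-level variance.

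**Working it through.** **Inputs** (Participants): n = 100 per arm, mean μ = 1–2, variance V = 4, correlation r = 0.80, α = 0.05, power 80%. Sidedness is not stated. The detectable difference is (z for α + z for power) × √(2 × Var(contrast)/n), with multiplier 1.960 + 0.842 = 2.802 two-sided or 1.645 + 0.842 = 2.486 one-sided (from unrounded z values).

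**1. Reproducing 0.44.**

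- Mean of two follow-ups minus baseline: Var = 1.5 × 4 × 0.2 = 1.2, SE = √(2.4/100) = 0.155. Two-sided detectable difference 2.802 × 0.155 = 0.434; power at 0.44 is 81.1%. This reproduces.
- 6 months minus baseline: Var = 2 × 4 × 0.2 = 1.6, SE = 0.179. One-sided 0.445, which also reproduces. Two-sided 0.501, with 69.1% power at 0.44, which does not.

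**2. Within-person variance.** The planning inputs give V(1 − r) = 4 × 0.2 = 0.8. With a stable mean, a Poisson mixed model gives V = μ + between-person variance, so within-person variance is at least μ and r is at most 1 − μ/V. Random slopes would only add to the within-person part. The model therefore implies 1.25 to 2.5 times the planned value. A correlation of 0.80 would need V = 5, 7.5 or 10 at μ = 1, 1.5 and 2, or μ = 0.8 at V = 4. Since 4 is given as an upper value, a smaller variance at r = 0.80 widens the gap.

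**3. If the Poisson model is right.** Replace V(1 − r) by μ: Var = 1.5μ (averaged) or 2μ (6 months). Two-sided results:

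| Mean | Largest r at V = 4 | Averaged: detectable difference | Averaged: power at 0.44 | 6 months: detectable difference | 6 months: power at 0.44 |
|---|---|---|---|---|---|
| Plan's inputs | 0.80 assumed | 0.434 | 81.1% | 0.501 | 69.1% |
| 1 | 0.75 | 0.485 | 71.9% | 0.560 | 59.5% |
| 1.5 | 0.625 | 0.594 | 54.5% | 0.686 | 43.5% |
| 2 | 0.50 | 0.686 | 43.5% | 0.792 | 34.3% |

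Example, mean 1.5, averaged: SE = √(2 × 2.25/100) = 0.212; 0.44/0.212 − 1.96 = 0.11, so power is about 54%. On the log rate-ratio scale that the model uses, power for the 6-month contrast is lower still: about 48%, 37% and 30%, confirmed by gamma-Poisson simulation.

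**4. If the planning values are right.** Poisson standard errors are too large by √(μ/0.8) = 1.12, 1.37 and 1.58. The true type I error is then about 2.8%, 0.7% and 0.2%, and power at 0.44 on the averaged contrast falls to about 74%, 56% and 40%.

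**5. If counts are over-dispersed within persons.** At V = 4 this happens when the true correlation is below 0.75, 0.625 or 0.50 for means of 1, 1.5 and 2. The outreach items could have this effect: under Data collection, up to ten are ticked only after a positive contact question, so ticks arrive together. Illustration with assumed inputs: 55% with contact, then Binomial(10, 0.30). The mean is 1.65 and the variance 0.55 × 2.1 + 9 × 0.55 × 0.45 = 3.38, so the break-even correlation is 1 − 1.65/3.38 = 0.51. Simulated type I error, from a two-occasion conditional Poisson test, was 15.7% at correlation 0.09, 6.2% at 0.47 and 4.0% at 0.56.

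**The case against.** The strongest reply is that the calculation is declared to be a simplification, that 0.44 follows from its own inputs, and that model details belong in an analysis plan that is not shown. The first two points are true. They do not cure the problem, because the approximation errs towards optimism at every mean in the stated range. The third does not apply, since the article itself fixes both the distribution and the planning inputs.

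Several stronger readings a reader might infer are not supported:

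- **That variance 4 contradicts a Poisson model with mean 1–2.** It does not. Random effects can supply the remaining 2–3 units, which is over-dispersion of the kind the article describes. The conflict arises only when correlation 0.80 is added. It is slight at mean 1 (0.75 against 0.80) and large at mean 2 (0.50).
- **That power falls from 80% to 34–59%.** Those figures use the two-sided 6-month contrast, which gives only 69% even on the protocol's own inputs. Part of that fall comes from contrast and sidedness. The like-for-like comparison is 81% against 72%, 54% and 44%.
- **That the type I error is inflated.** This needs a correlation well below the planned 0.80 and inputs the protocol does not give. The ten help-seeking items have no contact question, and the illustration used two occasions rather than three. Under the planning values the test is conservative.
- **That the model is a random-intercept model.** The article does not say so. The conflict does not depend on it, because extra random effects can only raise the within-person variance above the mean.

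**Conclusion.** The point holds as an inconsistency between the planning inputs and the primary model. A mean of 1–2, a variance of up to 4 and a correlation of 0.80 cannot all hold under the Poisson mixed model. If that model is right, power at 0.44 is about 72%, 54% and 44% for means of 1, 1.5 and 2, and the detectable difference is 0.49–0.69 on the averaged contrast or 0.56–0.79 at 6 months. This assumes two-sided 5%, 100 per arm, a mean stable apart from the added 0.44, no dropout and no clustering by course.

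It does not follow that the trial cannot detect a small effect: less than one behavior remains detectable in every scenario above. Nor does it follow that either the model or the power claim has been shown to be wrong in itself. What the documents support is that they do not fit together. Loss of power if the planning values are true follows from the protocol's own numbers; type I inflation is only a possibility.

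**What to change.** 1. Restate the detectable difference or power under the analysis model, using a correlation that model permits, and name the contrast and sidedness. For example: with 100 per arm, two-sided 5%, 80% power and the mean of both follow-ups minus baseline, 0.49, 0.59 or 0.69 behaviors for means of 1, 1.5 and 2 (variance 4; correlation 0.75, 0.625 and 0.50).
2. Keep the log-link count model, but do not let primary inference rest on variance equal to the mean. Use participant-level robust (sandwich) or bootstrap standard errors, or a free dispersion parameter. The dispersion should be able to fall below as well as above the Poisson value: a negative binomial model or an observation-level random effect covers only the over-dispersed side.

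Clustering by training course is a separate matter and is not addressed by this change. The cost is a less favourable stated precision and slightly more analysis work. No new data are needed.

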## Methods/Design

A multi-centre, randomized, evaluator-blinded, two-group parallel design will be adopted, comparing the impact of the Beyond Silence (CBE) program with mental health literacy training. A parallel group design will be adopted where participants in both groups will receive 12 hours of group-based education, but the content, schedule and format will be different. The 1:1 randomization sequence will be generated off site (in Calgary) using the software Stata. Randomization will occur in four blocks of 26 and four blocks of 24, leading to n = 100 in each assignment group and exactly 12 or 13 participants in each assignment. The sequence will not be shared with the investigative team, who will instead determine each participant’s assignment using an interactive web-based system. Mental Health First Aid training (MHFA) will serve as the control group since its efficacy is already well established in the literature [32]. The “Beyond Silence” approach is novel, and based on best practice principles, but research is needed to determine whether it is effective. Help seeking/outreach behavior, mental health literacy, and mental health stigma will be assessed at 3 month intervals: at baseline, after completion of the program and at 3 months follow-up. The study protocol was registered in May 2014 on ClinicalTrials.gov (ID#: NCT02158871). Ethical approval was also obtained through the Hamilton Integrated Research Ethics board.

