### Interventions

The ***“Beyond Silence” CBE intervention*** program will be co-led by trained peer educators who have personally experienced mental ill health and recovery. The peer educators will be employees within the organization who not only have personal experience with mental ill health (either themselves or a close family member), but are good communicators and credible leaders within the organization. They will be recruited and trained to effectively teach the content, share their personal experiences, and facilitate discussion. Four employees (plus one “back-up” person) will contracted for approximately 125 hours over the course of the two years (including training and support sessions), with two peer educators facilitating each Beyond Silence group program. The Beyond Silence curriculum was designed to address the unique needs of the organization and is based on; a) pilot data from the initial qualitative phase of the project [33], b) a review of programs utilized in other workplaces, and c) best practice principles of contact based education and knowledge translation. It will include a series of 6 in-person group sessions (plus 5 online sessions) designed to provide information, diminish anxiety and promote empathy; all best-practice dimensions of CBE [28]. Sessions will be held weekly, alternating between a 1.5-2 hour in-person session and an online learning opportunity. The in-person sessions will combine information sharing and discussion, using workplace-based vignettes to build mental health literacy, reduce stigma and increase confidence and skill in reaching out to seek/offer help. The online “virtual” sessions using a secure, online platform, will encourage self-directed exploration of community and online resources and provide an opportunity for online dialogue that can be accessed at any time or place. All participants will receive a program handbook with the core content and worksheets. Each Beyond Silence program will be offered over a three month period. Over the course of the project, eight programs will be offered with approximately 12–13 participants per program.

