The control group intervention is Mental Health First Aid (MHFA), a standardized, twelve-hour educational program designed to teach participants how to recognize the early warning signs of mental illness, how to provide initial help to someone in a mental health crisis, and how to support people who are developing mental health problems [25]. It is an evidence-based approach, with several RCT’s documenting significant increases in mental health literacy, decreased social distance, and increased reports of helping behaviors [24,34,35]. The program originated in Australia, but is being implemented across Canada, under the leadership of the Mental Health Commission of Canada. A staff member in each organization who has been trained through the 5-day instructor-training program will be seconded to facilitate the program within their organization. Each course will be offered as two full days, typically one week apart. All participants will receive a training manual, which covers all of the content of the standardized, module-based curriculum. Over the course of the project, eight courses will be offered with approximately 12–13 participants per course.

The location and specific dates/times for the sessions will be customized for each group in order to facilitate participation and maximize response rate, but groups will scheduled to start in regular intervals over the course of the two years (fall, winter, spring, fall). The Beyond Silence programs will be scheduled in the early evenings (outside of regular work hours), and the MHFA programs will be scheduled for two full days, one week apart.

Monthly meetings will be scheduled with the peer educators to provide support, address any questions/concerns, and maximize fidelity to the principles of the Beyond Silence program. A fidelity measure was designed to track adherence to structural elements (6 items), as well as content and process principles (10 items) of the program, using a 4-point Likert-type rating scale. Fidelity assessment will occur between sessions 3 and 5, and will be completed by a participant observer who is part of the core project team. Ratings will be discussed with peer educators at monthly meetings, with any departures from the established principles noted and explained, including plans (if applicable) to improve adherence. Fidelity to the MHFA program principles will be monitored through MHFA Canada, as per their internal processes.

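### Both arms are taught in training groups of 12–13, but neither the described primary model nor the precision estimate allows for correlation within those groups; if it exists, the primary test is anticonservative and the stated 0.44 is too favourable

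*Protocol article*

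**What the plan says.** Methods/Design (protocol article) states that "participants in both groups will receive 12 hours of group-based education". Randomization is of individuals, in eight blocks of 24 or 26, so each block sends 12 or 13 people to each arm. Interventions plans eight Beyond Silence programs and eight MHFA courses of about that size, which makes 16 training groups.

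Facilitators are few. Beyond Silence contracts four peer educators and one back-up, "with two peer educators facilitating each Beyond Silence group program". For MHFA: "A staff member in each organization who has been trained through the 5-day instructor-training program will be seconded to facilitate the program".

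For the primary outcome, a count of help-seeking and outreach behaviors at three surveys, Data analysis specifies a Poisson generalized linear mixed model without additional covariates and says of it: "This is a standard approach that accounts for over-dispersion in the Poisson model arising from the repeated measurements". No other source of dependence is named.

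Participants gives the precision estimate. "The plan is to enroll 200 employees in total, with 100 participants in each group". The other inputs are a variance of 4 ("assuming that the variance averaged over groups and occasions might be as high as 4") and a test-retest correlation of 0.80. The result is 80% power for an "average change over 6 months of as little as 0.44 behaviors". The 0.80 is described as consistency within groups, but its gloss as test-retest shows that it is a within-person quantity and not an allowance for training groups.

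**The concern.** Individual randomization makes participants independent at baseline. It does not keep them independent once they are taught together. Members of one Beyond Silence program share two facilitators, their personal accounts, the discussion and an online forum for three months. Members of one MHFA course share an instructor for two days. If some groups go better than others, later behavior will be more alike within a group than between groups.

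A model that knows only about repeated surveys on one person attributes that group-level variation to chance differences between 200 independent people. The standard error of the arm contrast is then too small, and a few strong or weak groups can look like a program effect. Data analysis lets the significance of the treatment term in this model answer the first research question, so the trial's main conclusion would carry the error. The sample-size justification shares the same assumption.

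**Working it through.** **Inputs from the document:** 100 per arm; variance σ² = 4; test-retest correlation ρ = 0.80; 80% power; p < .05 (sidedness not stated); 8 + 8 training groups, mean size 12.5. **Assumption:** the training-group ICC of the change in outcome, taken from 0.01 to 0.10, because the document gives none.

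**Step 1: reproduce 0.44.** Detectable difference = (z for alpha + z for power) × √(2V/100), where V is the variance of one person's change.

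- Mean of the two post-baseline surveys minus baseline: V = 4 × (1 − 0.8) × 1.5 = 1.2. Two-sided: (1.960 + 0.842) × √0.024 = 0.434, with 81% power at 0.44.
- Baseline to 6 months: V = 2 × 4 × (1 − 0.8) = 1.6. One-sided: (1.645 + 0.842) × √0.032 = 0.445. Two-sided: 0.501, with 69% power at 0.44.
- Baseline-adjusted analyses (ANCOVA), two-sided: 0.475 with one post-baseline survey, 0.404 with the mean of two.

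The two readings that return 0.44 (0.434 and 0.445) do so with ICC = 0. The first is two-sided and is used below.

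**Step 2: add clustering.** Design effect DE = 1 + (12.5 − 1) × ICC. The true standard error is √DE times the naive one. The actual type I error of a nominal 5% two-sided test is 2 × [1 − Φ(1.96/√DE)]. The detectable difference is 0.434 × √DE. For example, at ICC 0.05, DE = 1 + 11.5 × 0.05 = 1.575, √DE = 1.255, type I error is 11.8%, and the detectable difference is 0.434 × 1.255 = 0.545.

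| ICC, both arms | DE | Type I error | Detectable difference | Power at 0.44 | Power at 0.44, 14 df |
|---|---|---|---|---|---|
| 0 | 1.000 | 5.0% | 0.43 | 81% | 75% |
| 0.01 | 1.115 | 6.3% | 0.46 | 77% | 71% |
| 0.02 | 1.230 | 7.7% | 0.48 | 73% | 66% |
| 0.05 | 1.575 | 11.8% | 0.55 | 62% | 56% |
| 0.10 | 2.150 | 18.1% | 0.64 | 49% | 44% |

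The last column uses 16 groups − 2 arms = 14 degrees of freedom. The power columns assume a valid test, that is, one using the true standard error. Simulating 8 + 8 groups of 12 or 13 (40,000 runs per ICC) gave type I errors of 6.2%, 7.7%, 11.8% and 18.4% for the four positive ICCs.

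**Step 3: clustering in Beyond Silence only.** The variance of the contrast is then inflated by the average of the two arms' design effects. At ICC 0.05 this is (1.575 + 1)/2 = 1.29, giving a type I error of about 8.4%. At ICC 0.02 it is (1.23 + 1)/2 = 1.115, giving about 6.3%.

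**The case against.** **The inflation is conditional.** A reader might infer that the standard errors are certainly too small. The document does not support that: it gives no ICC, and the outcome is each employee's own service use and help to co-workers, not something done in the training room. At ICC 0.01 the type I error is only 6.3%. This objection stands, and the claim has to be put as an if.

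**The arms differ.** Discussion and prolonged contact are the intended mechanism of Beyond Silence. MHFA is a standardized modular course over two days. One ICC for both arms may overstate the problem, hence step 3. This stands too.

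**Some variation cancels.** Intake and organization effects shared by both arms of a block drop out of the contrast, and leaving block unfitted makes the standard error slightly conservative. That is correct, but it does not touch variation specific to one training group.

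**The article is condensed.** It lists no random effects, and the sentence on over-dispersion describes a general property of mixed models. A fuller analysis plan might contain a group term. What remains is that the article itself names the source of dependence and gives a precision figure without a clustering input. One could reach 0.44 by pairing the 0.404 ANCOVA result with an ICC of about 0.016, since (0.44/0.404)² = 1.186 and 0.186/11.5 = 0.016. The text mentions neither.

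**A larger power loss is tempting.** Starting from the two-sided baseline-to-6-month contrast, ICC 0.05 moves the detectable difference from 0.50 to 0.63 and leaves 50% power at 0.44. A reader might blame clustering for the whole fall from 80%. That contrast has only 69% power with no clustering at all; the gap between 0.50 and 0.44 is a separate question of contrast and sidedness.

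**Conclusion.** The omission is real and enters both the described primary model and the precision figure. If outcomes correlate within training groups, the primary test is anticonservative and 0.44 is too favourable. A positive correlation is plausible because discussion and shared facilitators belong to delivery, most clearly in Beyond Silence. Its size is not known from the document. Over the assumed ICC range of 0.01 to 0.10 in both arms, type I error runs from about 6% to 18% and power at 0.44 from 77% down to 49%, before any correction for few groups. The figures rest on the linear approximation that the article itself uses, a two-sided test and the contrast in step 1. I am confident of the omission and only moderately confident of the amount of inflation.

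A reader might also infer that a training-group term would settle the facilitator question. It would not. Eight Beyond Silence programs with two places each are shared among four peer educators, about four programs each if divided evenly, and the eight MHFA courses among about one instructor per organization. A facilitator effect that recurs across groups remains mixed with the arm effect.

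**What to change.** - Add a random effect for training group (16 levels) to the primary model and the mediator models. It should act on the post-training surveys, because groups have not met at baseline. Let its variance differ by arm if the data can estimate this.
- Use small-sample degrees of freedom, about 14. An uncorrected cluster bootstrap with eight groups per arm is not an adequate substitute.
- Restate the detectable difference over ICC 0.01–0.10, naming the contrast and the sidedness.
- Limit the conclusion to the facilitators used.

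This changes the analysis wording and not the conduct of the trial. Attendance is recorded at each session, so group membership should be known. The price is wider confidence intervals and a less favourable stated precision: even with an ICC of zero, 14 degrees of freedom lower power at 0.44 from 81% to 75%.

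### The decision rule for Research Question 1 names the treatment-group term in a model that counts baseline as an outcome, while the hypothesis and sample size concern a difference in change

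*Protocol article*

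**What the plan says.** Surveys are taken "at baseline, after completion of the program and at 3 months follow-up" (Methods/Design), that is at 0, 3 and 6 months. The Data analysis section hypothesizes that "help-seeking behavior will increase from baseline to 3 and 6 months by a greater amount in the Beyond Silence group" than in the control group. The sample-size text under Participants works on the same quantity: "we have an 80% chance of finding a significant (p < .05) difference between the two groups in average change over 6 months", with a detectable difference of 0.44 behaviors. The abstract likewise describes the primary analysis as a comparison of changes over time.

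For the model, the Data analysis section states: "Overall tests of the change across all three measurements are available from generalized linear mixed-effects analysis", with the behavior count treated as Poisson. It then sets the decision rule: "the statistical significance of treatment group in this model will be used to address the first research question". It adds that "the primary analysis will not include additional covariates". The only interactions it mentions are exploratory ones, "interactions between these covariates and treatment group".

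**The concern.** In a repeated-measures model with baseline among the outcomes, the treatment-group term is not in general the difference in change. Its meaning depends on the other terms:

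- **Group and time, no interaction.** The term is the group gap averaged over three surveys. One of these precedes training, so its expected gap is zero and it dilutes the effect. Stable between-person variation, which a change contrast removes, stays in the standard error.
- **Group-by-time included, baseline as reference.** The group coefficient is the baseline gap, which carries no information about the programs.
- **Baseline means constrained equal.** Treatment enters only after baseline, and its test is then the right one.

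The article does not say which model applies, and the wording is closest to the first. At stake is the trial's main inference: a real advantage of the size planned for could go undetected, or the contrast could be chosen after the data are seen. The exploratory modifier analyses share the ambiguity, because a covariate-by-group term in such a model need not describe modification of change.

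**Working it through.** **Inputs.** From Participants: variance 4, test-retest correlation 0.80, 100 per group, 0.44 behaviors, 80% power, p < .05 with sidedness not stated. Assumed here: the same correlation between every pair of surveys, no dropout (no figure is given), and no clustering by course group. Figures are on the mean-count scale of the plan's linear approximation.

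**Formulas.** With V the per-person variance of the quantity compared, SE = √(2V/100). Detectable difference = (z_α + 0.842) × SE, where z_α is 1.960 two-sided or 1.645 one-sided. Two-sided power = Φ(δ/SE − 1.960).

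**Reproducing 0.44.**

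- Mean of both follow-ups minus baseline: V = 1.5 × 4 × (1 − 0.80) = 1.2 and SE = 0.155. Detectable difference 2.802 × 0.155 = 0.434 two-sided.
- Baseline to 6 months: V = 2 × 4 × (1 − 0.80) = 1.6 and SE = 0.179. Detectable difference 2.802 × 0.179 = 0.501 two-sided, or 0.445 one-sided.

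So 0.44 is recovered as a contrast in change: two-sided on the averaged follow-ups, or one-sided to 6 months.

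**The group main effect on the same inputs.** The variance of a person's three-survey mean is V = 4 × (1 + 2 × 0.80)/3 = 3.467, so SE = 0.263.

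- Gap 0, 0.44, 0.44: expected effect 0.44 × 2/3 = 0.293; power = Φ(1.114 − 1.960) = 20%.
- Gap 0, 0.22, 0.44: expected effect 0.66/3 = 0.22; power = Φ(0.836 − 1.960) = 13%.

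**Two-sided power, side by side.**

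| Test | SE | Gap 0.44 at both follow-ups | Gap growing 0, 0.22, 0.44 |
|---|---|---|---|
| Group main effect, three surveys | 0.263 | 20% | 13% |
| Mean follow-up minus baseline | 0.155 | 81% | 57% |
| Baseline to 6 months | 0.179 | 69% | 69% |

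The 57% uses a mean follow-up gap of (0.22 + 0.44)/2 = 0.33: Φ(0.33/0.155 − 1.960) = Φ(0.17).

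For 80% power, the main effect needs a 6-month gap of 2.802 × 0.263/(2/3) = 1.11 if the gap is flat, or 2.802 × 0.263/0.5 = 1.48 if it grows linearly. To detect 0.44 it needs about 633 or 1,125 per arm respectively. A normal-model simulation (5,000 runs) gave 19.7% and 13.2% for the main effect and about 68% for baseline to 6 months.

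**Sensitivity to the correlation, 0.5 to 0.9.** Main-effect power stays between 12% and 25%. Baseline-to-6-month power runs from 34% to 94%, so the gap narrows as the correlation falls.

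**Poisson checks.** A random-intercept simulation (3,000 runs, mean 1.5, variance 4, gap 0.50 at both follow-ups) gave 24% for the group term and 53% for group by follow-up versus baseline. A rougher check with Poisson estimating equations (400 runs, gap reaching 0.44, assumed baseline means 0.8 and 1.5) gave 17–34% and 26–48%. With mean 1.5 and variance 4, the implied baseline correlation is 1 − 1.5/4 = 0.625, below the planned 0.80, which helps explain the smaller separation.

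**The case against.** The strongest reply is that the phrase is shorthand. The abstract, the sample-size text and the hypothesis all speak of change, and the sentence on overall tests of change comes shortly before the decision rule. A model with equal baseline means, or a joint test of all terms involving group, would make the rule sound, and the article excludes neither. It is also a condensed account, and exact fixed-effect terms are often left to a fuller document.

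Much of this stands. A reader might infer that the trial will certainly test the wrong quantity. The article gives no model equation, so that cannot be shown. A reader might also infer that the test has only its 5% false-positive rate whatever the programs do. That follows only if group-by-time terms are fitted and the baseline coefficient is then read as the treatment effect, which nothing in the text suggests. Nor should the full distance from 80% be blamed on this wording: 80% comes from a linear approximation, and in the Poisson checks the change contrast itself falls well short of it.

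What does not stand is that this is only a missing detail. The article states its primary decision rule, and the term named there does not, as written, match the hypothesis or the quantity used for the sample size.

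**Conclusion.** The point holds as a conflict between the stated decision rule and the stated hypothesis and power basis. Intent is probably a test of change, but the wording permits tests of different quantities. Under the literal reading (group main effect over three surveys), two-sided power at 0.44 is about 20% if the gap is present at both follow-ups. The comparable figures are 81% for averaged change and 69% for change to 6 months. If the gap grows linearly, the figures are 13%, 57% and 69%. These rest on variance 4, correlation 0.80, 100 per arm, complete data, no clustering and the linear approximation. Under a Poisson model the loss is smaller but in the same direction.

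**What to change.** Replace the decision-rule sentence with one that names the contrast, for example: *The primary test of Research Question 1 is the group-by-time contrast comparing the groups on change from baseline, averaged over the 3- and 6-month surveys, with baseline means constrained equal across groups.* Adjusting for baseline is an acceptable alternative; the sentence on covariates should then say that baseline is the exception.

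State the sidedness and keep the contrast consistent with the sample-size text. The averaged contrast matches a hypothesis that names both 3 and 6 months, and it reproduces 0.44 two-sided. If baseline to 6 months alone is preferred, restate the detectable difference as about 0.50 two-sided (about 0.475 with baseline adjustment: V = 4 × (1 − 0.80²) = 1.44).

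Describe the exploratory modifier analyses as covariate-by-group effects on change, that is covariate-by-group-by-time terms.

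The cost is a few sentences of wording, settled before outcome data are examined. No new data or participants are needed to correct the rule.
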